#### Adherence Support

The package of adherence support offered will include data-driven counseling and interactive weekly text messaging. We will assess adherence by means of a composite of INR values above and below the therapeutic range, TTR, and self-report.

#### Root Cause Analysis

Root cause analysis (RCA) will be undertaken in all patients on warfarin at the INR clinic or hospital who are seen with serious thrombotic or hemorrhagic events. An RCA committee at each clinic, comprising a multidisciplinary team of 4-6 individuals, will review each case using the 9-step process of RCA described by Charles et al [9]. Root causes and corrective actions developed will be categorized on a standardized RCA data collection form to ease analysis [10]. The results of each RCA (root causes, contributing factors, and corrective actions) will be shared with staff at the clinic. Findings of RCA will be discussed at monthly study meetings to inform the overall warfarin bundle implementation (in areas such as adherence, monitoring, and education).

### Process-Centered Components of Warfarin Bundle

#### Point-of-Care Testing

We will make point-of-care INR testing a central part of improving the clinical pathway. Currently, some patients must wait at least a day to receive their INR result and subsequent dosing guidance.

#### Staff Training

We will include co-design workshops discussing the rationale for the bundle and likely implementation issues with a team of clinicians involved in the provision of anticoagulation services. Training will be personalized based on local requirements, depending on the site and staff involved.

#### Cocreation of Patient Education and Training

Co-design workshops for the development of training material to be used in patient education will bring together patient or community representatives, health care staff, the research team, and a representative from policy makers. Different methods will be discussed and explored by the cocreation team in collaboration with representatives from the community and health care workers to ensure they are applicable to the local setting.

### Participant Eligibility Criteria

Participants will be included in the study if they are adults aged 18 years or older; newly initiated on warfarin anticoagulation for the first time for venous thromboembolism, atrial fibrillation, or valvular heart disease; provide informed consent; and are willing to comply with study procedures. We will exclude participants who are on treatment for tuberculosis, pregnant women, and patients who have had more than one dose of warfarin. For the retrospective study, we will include adults newly initiated on warfarin for more than 3 months before we implement the trial.

### Sample Size and Power Calculations

To calculate our sample size, we assumed TTR in current practice to be 0.41 (based on average TTR from our audit) and the SD of TTR to be 0.25 on the basis that anticoagulation control before implementing the bundle is better than that found during the audit (0.33), due to the introduction of the clinical algorithm in a preceding pilot implementation study. We also assumed a Type I error rate of 0.05, power of 80%, and that the retrospective and prospective ratio would be 2:1. To achieve a minimum clinically important difference of 0.07 (ie, improvement from 43% to 50% TTR), we calculated that we would need at least 304 retrospective and 152 prospective participants (including a 10% contingency for losses to follow-up). This is in total across both Uganda and South Africa.

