**Figure 2 figure2:**
[figure not shown]
Flow diagram of prospective recruitment and follow-up. INR: international normalized ratio. War-PATH: Warfarin Anticoagulation in Patients in Sub-Saharan Africa.

**Table 1 table1:** Participant groups.

	Prospective	Retrospective
Population	Participants starting warfarin and consenting to implementation bundle	Historical controls started on warfarin at anticoagulation clinics where warfarin bundle is implemented
Sample size	152	330
Inclusion criteria	New initiators on warfarin Indication for warfarin is VTE^a^, AF^b^, or VHD^c^ Adults (ie, 18 years or older) Participant is resident in and willing to be followed up at a health facility where follow-up is feasible	New initiators on warfarin Indication for warfarin is VTE, AF, or VHD Adults (ie, 18 years or older)
Exclusion criteria	Pregnancy Received more than one dose of warfarin prior to recruitment Diagnosed with and currently on treatment for Tuberculosis	Pregnancy Diagnosed with and treated for Tuberculosis at time of warfarin initiation
Self-reported ethnicity	Yes	No
EQ-5D-3L questionnaire	Yes	No
Participant expenses tool	Yes	No
Baseline INR^d^	Yes	Yes
INRs during the first 3 months of treatment	Yes	Yes
All adverse events	Yes	Yes
Hospital admissions	Yes	Yes

^a^VTE: venous thromboembolism.

^b^AF: atrial fibrillation.

^c^VHD: valvular heart disease.

^d^INR: international normalized ratio.

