### Data Analysis Plan

For the prospective and retrospective studies, all statistical analyses will be undertaken in R. For determining percentage time in target range for each participant, all INR measurements during the first 12 weeks as well as the first INR measurement after the 12-week time point will be used, and the method of Rosendaal et al [14] will be applied. Percentage TTR will be compared between the prospective implementation group and the retrospective standard of care group using the Student *t* test. Time to achieving target INR (defined as the first of at least two INR measurements in range at the same dose) will be compared between the prospective and retrospective groups using the log-rank test (to compare the survival distributions of the 2 groups, and these will be calculated using the Kaplan-Meier estimator). Adverse events will be compared between the 2 groups using a chi-square test. A significance threshold of *P*<.05 will be applied.

The primary analysis will include all participants who remain in the project for at least 2 weeks (14 days). Our primary analysis will include only patients who have at least two weeks’ follow-up, since it is unlikely that those with less than 2 weeks’ follow-up will have sufficient information on INR measurements for TTR to be reliably estimated. A sensitivity analysis will be undertaken, including only participants who have completed 12 weeks (84 days) of follow-up.

We will also conduct both an intention-to-treat analysis (including all recruited patients) and a per-protocol analysis (excluding patients where health care provider decided to reject the dose recommended by the dosing algorithm). The project will follow national guidelines for best practice and be guided by local policy. Relevant data will be made openly available to other researchers in a timely way (after primary outputs are published) with as few restrictions as possible unless we are protecting intellectual property, respecting confidentiality, or honoring third-party agreements. The program management board will review access to data and will provide a governance mechanism.

We will perform a secondary analysis comparing the primary and secondary outcomes between retrospective controls from the pre–COVID-19 and COVID-19 periods to measure the impact of the pandemic on anticoagulation control.

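### The stated 304 + 152 sample is the requirement before losses, not one that includes the 10% contingency; the control target and the baseline TTR are also given inconsistently

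*Protocol article*

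**What the plan says.** All inputs stand in one paragraph of the Protocol article, Sample Size and Power Calculations.

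- Error rate, power and allocation: "We also assumed a Type I error rate of 0.05, power of 80"%, with a 2:1 ratio of retrospective to prospective participants.
- Baseline: "we assumed TTR in current practice to be 0.41", taken from the group's own audit.
- SD of TTR: 0.25. The reason given is that "anticoagulation control before implementing the bundle is better than that found during the audit (0.33"), following the introduction of the algorithm in a pilot.
- Effect: a minimum clinically important difference of 0.07, glossed as "improvement from 43% to 50% TTR".
- Result: "we would need at least 304 retrospective and 152 prospective participants (including a 10% contingency for losses to follow-up").

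Table 1 (Participant groups) lists the prospective and then the retrospective size as "Sample size 152 330". The Data Analysis Plan says percentage TTR is "compared between the prospective implementation group and the retrospective standard of care group using the Student" t test, without giving sidedness. Results reports that recruitment stopped with 167 prospective participants.

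**The concern.** A sample size that includes a 10% allowance should exceed the evaluable requirement by about a tenth. Here the stated number sits almost exactly on the evaluable requirement, so the plan claims a margin it does not have. Once the plan's own expected loss occurs, the primary comparison falls below the stated 80% power.

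The two other mismatches make the calculation hard to reconstruct. A reader cannot tell whether 304 or 330 control records are to be abstracted, or whether the target effect starts from 41% or 43%. The article says the findings will be used to design a larger multisite trial, so the figures may be reused.

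**Working it through.** **Inputs.** From Sample Size and Power Calculations: d = 0.07, SD = 0.25, alpha = 0.05, power 0.80, ratio 2:1. Two-sided testing is assumed.

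**Step 1: evaluable requirement.** For a 2:1 comparison of means:

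- smaller arm n = (1 + 1/2) × (1.960 + 0.842)² × SD²/d² = 1.5 × 7.85 × 0.0625/0.0049 ≈ 150.2
- larger arm = 2 × 150.2 ≈ 300.3

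Rounded up, this is 151 + 301. With the noncentral t distribution, the smallest 2:1 design reaching 80% is 151 + 302.

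**Step 2: compare with the stated figure.** The stated 152 + 304 is within 1% of Step 1. With no loss, its standard error is 0.25 × √(1/304 + 1/152) = 0.0248, the noncentrality is 0.07/0.0248 = 2.82, and power (t) is 80.3%. It is therefore the number before any inflation.

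**Step 3: add the contingency.**

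- Dividing by 0.9: 151/0.9 = 167.8 → 168; 302/0.9 = 335.6 → 336
- Multiplying by 1.1: 151 × 1.1 = 166.1 → 167; 302 × 1.1 = 332.2 → 333

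Either way about 10% more is needed in each arm than the text states.

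**Step 4: could another reading give 152 + 304 with the contingency included?**

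- One-sided alpha: 119 + 237 evaluable, 133 + 264 after dividing by 0.9. No.
- Difference 0.09 (0.41 to 0.50): 91 + 182 evaluable, 102 + 203 after dividing by 0.9. No.

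**Step 5: power after 10% loss** (d = 0.07, SD = 0.25, two-sided t). 152 × 0.9 ≈ 137, 304 × 0.9 ≈ 274, 330 × 0.9 = 297, 167 × 0.9 ≈ 150.

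| Starting numbers | Loss | Prospective / control analysed | Power |
|---|---|---|---|
| 152 / 304 (text) | none | 152 / 304 | 80.3% |
| 152 / 304 | both arms | 137 / 274 | 76.1% |
| 152 / 304 | prospective only | 137 / 304 | 77.5% |
| 152 / 330 (Table 1) | none | 152 / 330 | 81.3% |
| 152 / 330 | both arms | 137 / 297 | 77.2% |
| 152 / 330 | prospective only | 137 / 330 | 78.5% |
| 167 recruited, 304 controls | prospective only | 150 / 304 | 80.0% |
| 167 recruited, 330 controls | both arms | 150 / 297 | 79.7% |
| 167 recruited, 330 controls | none | 167 / 330 | 83.7% |

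**Step 6: the two inconsistencies.**

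- Controls: 304/152 = 2.00, but 330/152 = 2.17, so Table 1 does not keep the stated ratio. The 330 is near an inflated control number (333 to 336) while the 152 is uninflated; the article does not explain the 330.
- Baseline: 0.50 − 0.43 = 0.07, but 0.50 − 0.41 = 0.09, and 0.41 + 0.07 = 0.48. With d and SD fixed, the baseline does not enter the formula in Step 1.

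**The case against.** The strongest reply is that little hangs on this in practice, and much of it stands.

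- **The shortfall is small and depends on where losses fall.** Controls come from a record review, where an unusable chart can perhaps be replaced, and the 10% is described as being for losses to follow-up. The primary analysis also keeps anyone with at least 14 days in the project, so a participant lost after week 2 still counts. The 76% figure is therefore the lower end of a range, not the single result.
- **Recruitment overtook the error.** The 167 recruited is what the inflated calculation asks for (167 to 168), and the text says the numbers are a minimum.

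Neither point makes the sentence about the contingency true.

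A reader might also infer more than the documents support:

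- *That the baseline and Table 1 mismatches cost power.* They do not. The baseline does not enter the calculation, and reading the effect as 0.41 to 0.50 would raise power at 152/304 to about 95%. Table 1's extra controls raise power from 80.3% to 81.3% before losses.
- *That the 167 recruited give 80% only with about 330 controls.* With 10% prospective loss, 150/304 already gives 80.0%. About 330 matters only if control records are lost as well and not replaced.
- *That the SD of 0.25 is an error.* It is a disclosed assumption with a stated, if thin, reason. Mean TTR does not determine the spread between patients, standardised dosing could narrow it, and nothing in the article shows 0.25 to be wrong.

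**Conclusion.** The point holds as an arithmetic error in the stated plan, with two reporting inconsistencies beside it. The 304 + 152 does not include the 10% contingency it is said to include. If 10% are lost from the primary analysis, the planned numbers give about 76% to 77.5% power, or about 77% to 78.5% with Table 1's controls: a shortfall of about 1.5 to 4 percentage points from 80%. This rests on a two-sided test, d = 0.07, SD = 0.25, and losses that actually leave the primary analysis set.

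The 304 versus 330 and 0.41 versus 43% contradictions are real and need reconciling, but do not themselves reduce power. The documents do not support saying that the study as recruited is materially underpowered under its own assumptions: at 167 prospective participants, power after 10% loss is close to 80%.

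**What to change.** 1. State 151 prospective and 302 retrospective as the evaluable requirement, and about 168 + 336 (dividing by 0.9) or 167 + 333 (multiplying by 1.1) as targets with the contingency. Alternatively, delete the contingency claim and give power after 10% loss as about 76% to 78%.
2. State that the test is two-sided, if it is.
3. Use one control number in the text and in Table 1, with a ratio that matches it.
4. Use one baseline throughout: 0.41 to 0.48, or 0.43 to 0.50. If 0.41 to 0.50 is meant, the difference is 0.09 and the calculation must be redone.
5. Report power at the recruited size: 167 prospective, about 80% after 10% prospective loss with 304 analysable controls, and 79.7% with 150/297.
6. Optionally, add a sensitivity figure at the audit value of 0.33, read as an SD: about 56% at 150/297. This would show dependence on the SD assumption; it does not correct an error.

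The cost is a change of wording and a slightly less favourable power figure for the planned numbers. At most some additional control records would be abstracted, if the team adopts the inflated control target. No further prospective patients are needed, and no estimate, test or analysis set changes.

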## Results

We started recruitment in June 2021 and stopped in August 2022, having recruited 167 participants. As of February 2023, data cleaning and formal analysis are underway. We expect to publish the full results by December 2023.

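### The 152 prospective and 304 retrospective participants are the numbers before the 10% loss contingency they are said to include; after 10% loss power is about 76–78%, and Table 1 gives a different control number (330)

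*Protocol article*

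**What the plan says.** The section Sample Size and Power Calculations gives these inputs:

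- Error rates: "We also assumed a Type I error rate of 0.05, power of 80"%. Whether the test is one- or two-sided is not stated.
- Effect: a "minimum clinically important difference of 0.07 (ie, improvement from 43% to 50% TTR").
- Spread: "the SD of TTR to be 0.25 on the basis that anticoagulation control before implementing the bundle is better than that found during the audit", that is, 0.25 in place of the audit's 0.33.
- Allocation: "the retrospective and prospective ratio would be 2:1".

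The result is that "we would need at least 304 retrospective and 152 prospective participants (including a 10% contingency for losses to follow-up"). The Data Analysis Plan names the Student t test for the primary comparison.

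Table 1 (Participant groups) has the row "Sample size 152 330", prospective first and retrospective second. The prospective number agrees with the text; the control number does not. The Results section reports that recruitment has closed, "having recruited 167 participants".

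**The concern.** A sample size that already includes a 10% contingency should be about one ninth larger than the number the test needs. Here the stated numbers almost coincide with the number the test needs, which suggests that the contingency was described but never added. If so, the claim of 80% power with 10% of participants lost is a property the stated sample does not have.

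Losses are to be expected under the plan itself. The primary analysis keeps only participants with at least 14 days of follow-up, and the withdrawal section lists several grounds for leaving the study. The conflict over the control number adds to this: a reader cannot tell which figure, 304 or 330, the power statement belongs to.

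**Working it through.** **Inputs** (sample-size section unless noted): difference d = 0.07; SD s = 0.25; α = 0.05, taken as two-sided; power 80%; two controls per prospective participant; Student t test (Data Analysis Plan); loss 10%.

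**Step 1. Reproduce the plan's figure.** With n prospective and 2n retrospective, the normal approximation is

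n = (1 + 1/2) × (1.960 + 0.842)² × s² / d² = 1.5 × 7.85 × 0.0625 / 0.0049 ≈ 150.2.

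This gives 151 prospective and 301 retrospective (2 × 150.2 = 300.3, rounded up). Exact power for the t test uses the noncentrality d / (s × √(1/n₁ + 1/n₂)) with n₁ + n₂ − 2 degrees of freedom:

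| Prospective / retrospective | Power |
|---|---|
| 150 / 300 | 79.8% |
| 151 / 302 | 80.05% |
| 152 / 304 | 80.3% |

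The smallest 2:1 pair that reaches 80% is 151/302. The plan's 152/304 is that requirement plus one prospective participant and two controls.

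**Step 2. Add the contingency.** Dividing by 0.9 gives 151/0.9 = 167.8 and 302/0.9 = 335.6, so about 168 and 336. Multiplying 152 and 304 by 1.1 instead gives about 167 and 334. Either way 152/304 is about 9% short.

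**Step 3. Look for a reading that rescues the sentence.**

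| Change to the inputs | Evaluable need | With 10% (÷ 0.9) |
|---|---|---|
| One-sided 0.05 | 119 / 238 | about 132 / 264 |
| Difference 0.09 (0.41 to 0.50) | 92 / 184 | about 102 / 204 |
| Difference 0.08 | 116 / 232 | about 129 / 258 |
| SD 0.33 (normal approximation) | 262 / 524 | 292 / 583 |

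None returns 152/304 with 10% included. The 0.09 row is there because the section gives the current TTR as 0.41 and then starts the improvement at 43%; only the 0.07 difference fits the stated numbers.

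**Step 4. Power after 10% loss.** The sample-size section does not say how the loss divides between the groups, so both cases are shown. Rounded, 152 × 0.9 = 137, 304 × 0.9 = 274, 330 × 0.9 = 297 and 167 × 0.9 = 150.

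| Starting numbers | Loss in both groups | Loss in prospective group only |
|---|---|---|
| 152 / 304 (sample-size section) | 137/274: 76.1% | 137/304: 77.5% |
| 152 / 330 (Table 1) | 137/297: 77.2% | 137/330: 78.5% |
| 167 recruited / 304 | 150/274: 78.5% | 150/304: 79.96% |
| 167 recruited / 330 | 150/297: 79.7% | 150/330: 81.0% |

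At 137/274 the difference detectable with 80% power is 0.0735 instead of 0.07.

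**Step 5. Ratio in Table 1.** 330/152 = 2.17, against the stated 2:1.

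**The case against.** The strongest reply has three parts.

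*Controls may not be lost in the usual sense.* They come from chart review without consent or recruitment, and more charts can be drawn. The figure of 76% is therefore the lower end. This stands, and it is why the range runs to 77.5% for 152/304. Control loss need not be zero, though: a sparse or short chart can fail the 14-day rule. Even with no control loss, 152/304 stays below 80%.

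*The study recruited 167.* This also stands as a practical matter: power after 10% loss is then between 78.5% and 81.0%. It describes what happened, however, and does not correct the stated basis for 152 and 304.

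*The section says at least 304.* That is a floor, and 330 satisfies it. A reader might take 304 and 330 as two rival stopping numbers for the chart review; the article states no stopping rule, so that does not follow. What remains is that 330 is unexplained and breaks the stated ratio.

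A reader might also note that 330 is 300 × 1.1 and that 167 is close to 152 × 1.1, and conclude that a contingency was applied in those places. The article links neither number to a contingency; it reports 167 only as the number recruited. Nothing here depends on that inference.

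**Conclusion.** The statement about the contingency is wrong as written. On the plan's own inputs, 152 and 304 are the numbers needed with no losses. At the planned size, the 10% loss that the plan allows for costs about 2.5 to 4 percentage points against the intended 80%, leaving about 76% to 77.5%, or 77.2% to 78.5% with Table 1's 330 controls. The conclusion assumes a two-sided test, but the one-sided reading does not reproduce the figures either. It takes the SD of 0.25 as given; whether that SD is right is a separate question.

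It would go too far to infer that the study as recruited is materially underpowered for this reason. With 167 prospective participants, power after 10% loss lies within about 1.5 points of 80% in every case shown. Nor does the point touch the validity of the t test or its confidence interval. It is an error in a stated design property, together with an unreconciled control number.

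**What to change.** In Sample Size and Power Calculations, state that 152 prospective and 304 retrospective are evaluable numbers without contingency (80.3% power), and that after 10% loss power is about 76% if both groups lose participants and about 77.5% if only the prospective group does. If targets with the contingency are given, show about 168 prospective and 336 retrospective. State that the test is two-sided. Use the same pair of numbers in that section and in Table 1; if 330 is kept, say where it comes from and that the ratio is then 2.17:1.

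The cost is a few sentences and one table cell. No new prospective participants are needed, and abstracting further control charts is optional. The downside is a slightly less favourable stated power.

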### Participant Recruitment

#### Prospective Study

We will recruit participants for whom a decision has already been made to initiate warfarin by the managing clinician (Figure 2). Decisions regarding whether or not patients require inpatient management for the initiation of warfarin are also made by the managing clinician. Participants who meet the inclusion criteria will be consecutively screened and enrolled in the study. In cases where participants are discharged from the hospital and referred for follow-up in a clinic close to their home or in the outpatient clinic of the hospital, the clinical records used at the recruitment site and those at the referral clinic will be reviewed.

The participant’s first 3 days of dosing will be driven by our new algorithm (Multimedia Appendix 1). Thereafter, dose revisions will be made according to current guidance outlined in the “Standard Treatment Guidelines and Essential Medicines List for South Africa” [11]. We will repeat the INR of participants every 2-4 days until stability is reached (2 consecutive INRs are in the target range). We will ensure close monitoring during the first 14 days of treatment. If stability is reached before the 14th day, we will continue to closely monitor the patient for the first 14 days. If the participant has not reached stability at 14 days, we will continue to monitor the participant with INRs every 2-4 days and adjust the warfarin dose until stability is reached. As we measure participants’ INR every 2-4 days over this period of close follow-up, we will propose dose adjustments to the clinical team based on INR results. The clinical team will still be free to override proposed adjustments based on their clinical expertise. Once stability is reached, we will perform one more INR 1 week later, after which the participants’ care will be fully handed back to the clinical team, and participants will continue to follow-up according to the local standard of care. We will continue to monitor and record all consecutive INR results for 3 months through direct contact with the participant at outpatient clinic, home visits, or electronic or paper record review.

We will collect the following data: age, sex, weight, height, indication for anticoagulation, target INR range, HIV status, recruitment center, all INR measurements during the first 3 months and the first INR after completion of the first 3 months, any dose changes, and any hospitalizations or adverse events (Table 1). We will also complete the EQ-5D-3L questionnaire and a patient-cost questionnaire to enable us to measure changes in quality of life and out-of-pocket expenditures, respectively.

We will test all patients for genetic variants that are determinants of warfarin dose and elucidate whether any patients who were poorly controlled on warfarin had a genetic profile which may have adversely affected their INR control. The genetic testing will be done at the end of the study and will also help with our future plans to validate a genetic dosing algorithm derived from our previous study’s analysis of genome-wide data. (South Africa HREC: 672/2017, Uganda: JC3017). We will also obtain consent to undertake genome-wide analysis in this patient group, which will help in future meta-analyses with our previous studies’ data to identify other genetic loci.

